#### Secondary Outcome Measures for Modern Innovative Solutions to Improve Outcomes in Rapid Access Asthma Clinic Patients

SABA use measured by the number of inhalers prescribed in 6 months pre- and post-MISSION clinic.Exacerbation frequency (defined as deterioration in symptoms requiring ≥30 mg prednisolone or equivalent for ≥3 days) during the 6 months pre- and post-MISSION.Frequency and severity of comorbidities.Frequency and type of allergy.Measurement of exhaled nitric oxide.Measurement and variation of lung function.Frequency and type of additional asthma control medication.Disease control and quality of life as assessed by ACQ and Asthma Quality of Life Questionnaire (AQLQ).Number of patients having measurement of forced expiratory volume in 1 second (FEV1)÷forced vital capacity (FVC) as a proxy for asthma control and severity.

#### Secondary Outcome Measures for Modern Innovative Solutions to Improve Outcomes in Rapid Access Asthma Clinic Patients and Primary Care Patients

Prescription of SABAs during last 6 months at baseline and 6 months.Exacerbation rates (defined as deterioration in symptoms requiring ≥30 mg prednisolone or equivalent for ≥3 days) during the last 6 months at baseline and 6 months.ED attendances, OOH contacts, and hospital admissions during the last 6 months at baseline and 6 months.Inhaled steroid doses and usage.Number of patients having measurement of FEV1÷FVC as a proxy for asthma control and severity.The sensitivity and specificity of the PRIMIS (Primary Care Information Services, University of Nottingham) Asthma Audit Tool in identifying the patients compared with gold standard specialist assessment and interrogation of primary care records.

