#### Description of Clinical Intervention and Treatment

Modern Innovative Solutions to Improve Outcomes in (MISSION) Severe Asthma is a novel service model pilot that took place in June and July 2014. MISSION was developed by asthma specialists from Portsmouth and Southampton asthma services.

The MISSION concept involved a “carousel clinic” which brings together all the assessments and investigations a patient requires into one clinic—the patient moved around each assessment or “investigation station” in a serial fashion. This allowed the research team to efficiently gather all the data required for both staff and the patient. This severe asthma patient journey was mapped and opportunities for improvement were identified such as earlier diagnosis by active case finding of at-risk patients, followed by a swift multidisciplinary assessment which meant patients could be seen sooner and assessed more effectively. Patients attending standard outpatient services undergo basic lung function, chest x-ray, and medical review. They are then referred for other tests or specialist opinions as required at different time-points

MISSION Severe Asthma identified patients with poorly controlled disease from general practice (GP) databases who had not been under secondary outpatient care in the last 12 months or who were not known to secondary care. The patients were then invited to Rapid Access Asthma Clinics (RAACs) for assessment at their GP surgery on a Saturday, at a time convenient for them. The clinics were held on Saturdays at a time better suited to the needs of asthma patients, many of whom are working or studying full-time.

The RAAC delivered a comprehensive asthma review including assessments of allergic status, airway inflammation, education, self-management planning, and smoking cessation leading to a written personalized 1-year asthma management plan for their GP providing clear treatment recommendations for those with uncontrolled but treatable asthma (see Figure 1). Treatment recommendations were in line with current asthma guidelines.

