#### Secondary Objectives

To conduct a prospective qualitative study exploring patients’ experience, understanding and perceptions of their asthma as well as views on MISSION.To explore the acceptability of MISSION as a service model for patients, staff, and the NHS.To retrospectively compare a clinical case finding approach in primary care with a computer-assisted interrogation on primary care records.To assess the health economic impact of the MISSION service.To phenotype patients with uncontrolled or severe asthma in primary care and gain more information about the asthma population in Wessex.To assess whether asthma comorbidities are assessed in standard outpatient care.To assess waiting times and times to specialist referral in MISSION and standard outpatient care.

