#### Secondary Outcome Measures for Modern Innovative Solutions to Improve Outcomes in Severe Asthma Assessment Clinic Patients and Outpatient Severe Asthma Clinic Patients

SABA use measured by the number of inhalers prescribed in 6 months pre- and post-MISSION or outpatient clinic.Exacerbation frequency (defined as deterioration in symptoms requiring ≥30 mg prednisolone or equivalent for ≥3 days) in 6 months pre- and post-MISSION or outpatient clinic.Health care usage costs for asthma and number of contacts (GP visits, emergency department [ED] or out-of-hour [OOH] attendances, hospital admissions, and emergency GP visits) over 6 months pre- and post-MISSION or outpatient clinic.Assessment of comorbidity (rhinosinusitis, anxiety and depression, dysfunctional breathing, gastro esophageal reflux, and obstructive sleep apnea) and method of assessment.Assessment of inhaler technique and recommendations for inhaler devices.Smoking cessation advice.Investigations performed during 6 months in secondary care, for example, full lung function, sputum induction, and performing a high-resolution CT scan of the chest.Time from GP referral to first clinic visit in secondary care.Time between first and second visit in secondary care.Time to appointment with other specialists for asthma-related comorbidity where indicated, for example, dietician, ENT, physiotherapist, psychologist, and CT imaging.Assessment of eosinophilic airways inflammation through measurement of fractional exhaled nitric oxide (FeNO).The frequency of nonattendance at clinic.

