### Screening and Enrollment

#### Quantitative

All patients from the RAACs and all primary care patients will be approached for consent to use their anonymized data from the MISSION clinics or from GP records for research purposes. No extra data for research purposes will be collected for the quantitative analysis from patients at MISSION assessments, asthma outpatient clinics, or GPs.

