#### Outpatient Severe Asthma Patients

Patients who attended outpatient clinics as new referrals in June and July will be approached by telephone after being identified from the clinic attendance list. If the patient is willing, they will be sent a PIS and consent form to send back to the study team in a stamped addressed envelope.

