### Modern Innovative Solutions to Improve Outcomes in Rapid Access Asthma Clinic Patients and Severe Asthma Assessment Clinic Patients

The MISSION service: The searches identified 1436 patients who were manually reviewed by the MISSION team and 460 patients met the criteria. All these patients were invited to the clinic; 125 were booked in, and 84 attended the RAACs, of whom 22 were identified for the SAACs.

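### PRIMIS specificity cannot be validly estimated in the RAAC and primary care groups, which were selected on the record-based reference; index-visit non-attendance has a related, smaller problem

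*Protocol article*

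**What the plan says.** The accuracy outcome is listed under the secondary outcome measures for RAAC and primary care patients: sensitivity and specificity of the PRIMIS "Asthma Audit Tool in identifying the patients compared with gold standard specialist assessment and interrogation of primary care records". It serves a secondary objective: "To retrospectively compare a clinical case finding approach in primary care with a computer-assisted interrogation on primary care records".

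The selection of these groups is described in several places:
- Description of Clinical Intervention and Treatment: "MISSION Severe Asthma identified patients with poorly controlled disease from general practice (GP) databases". These patients had also not been under secondary outpatient care in the previous 12 months, or were unknown to secondary care.
- Eligibility Criteria: primary care patients are those whom the record search classed as uncontrolled, who were invited and who did not come.
- Results, RAAC and SAAC patients: "The searches identified 1436 patients who were manually reviewed by the MISSION team and 460 patients met the criteria". All who met the criteria were invited; "125 were booked in, and 84 attended the RAACs, of whom 22 were identified for the SAACs".
- Screening and Enrollment, Quantitative: "All patients from the RAACs and all primary care patients will be approached for consent to use their anonymized data". No other primary care records are mentioned.

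For SAAC and outpatient severe asthma patients, a separate secondary outcome is "The frequency of nonattendance at clinic", with no visit or denominator given. Eligibility Criteria defines the SAAC group by attendance and the outpatient group by referral. Under Recruitment, however, outpatients are approached "after being identified from the clinic attendance list".

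**The concern.** Specificity is the proportion of reference-negative patients whom the tool correctly leaves out. It needs patients whom the reference standard calls negative. Here one component of the reference, interrogation of the primary care records, is also the entry criterion for both named groups. The other component, specialist assessment, was applied only to patients who had passed that criterion and then chose to attend.

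The secondary objective on case finding depends on this comparison. A figure computed in the named groups would be undefined, or would be read as the tool's specificity in an asthma register when it describes a small, pre-screened subset.

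Non-attendance has a similar structure. If a group is enrolled because its members attended, their non-attendance at that visit is fixed at zero.

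**Working it through.** The protocol states no precision or size calculation for either outcome. Its only design figure, 44 and 132 for exacerbation frequency, reproduces (SD 1.30 × √(1 − 0.5²) = 1.126, difference 0.64, two-sided 5%, 90% power, 3:1) and does not bear on this point.

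**PRIMIS, record reference**
- Inputs from Results: 1436 records manually reviewed, 460 meeting the criteria, 84 RAAC attenders.
- RAAC and primary care patients are both drawn from the 460, so reference negatives = 0 and specificity = x/0, undefined. Using the 369 reported in Results, Quantitative changes nothing: those patients are all reference-positive too.
- Reviewed but not meeting the criteria: 1436 − 460 = 976 (or 1436 − 369 = 1067). These patients appear in no eligibility group, analysis group or consent route.

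**PRIMIS, specialist reference**
- Verified patients: at most 84/460 = 18%, fewer if some decline consent.
- The share judged not uncontrolled is not reported. Assuming 10% to 30%, there are 8 to 25 negatives, every one already record-positive.
- Illustrative exact 95% intervals: 4/8 gives 16% to 84%; 20/25 gives 59% to 93%. Precision is poor, and the selection remains whatever the precision.

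**What the reviewed records could supply**
- If PRIMIS was run independently of the initial search and all 976 are true negatives, the half-width of a 95% interval for specificity is at most 1.96 × √(0.25/976) = 3.1 points. For assumed specificities of 0.70 to 0.95, exact half-widths are about 3.0 to 1.4 points.
- If PRIMIS was the initial search, all 1436 are tool-positive. Sensitivity is then 460/460 = 100% and specificity 0/976 = 0% by construction. Only positive predictive value is informative: 460/1436 = 32% (369/1436 = 26% on the other count).
- If k of the 976 were set aside for recent secondary care and not for controlled asthma, the negatives fall to 976 − k. The protocol does not give k.

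**Non-attendance**
- SAAC patients: 20 attended (Qualitative Data Collection), so index-visit non-attendance among those enrolled is 0/20 by definition. The same holds for outpatients taken from the attendance list.
- Second visits and appointments with other specialties are recorded in the notes review, so later non-attendance can be counted. As an illustration, 4/20 = 20% has an exact 95% interval of 5.7% to 43.7%.
- SAAC index visit from service counts: (22 − 20)/22 = 9.1% (1.1% to 29.2%), only if all 22 identified patients were booked and the 2 not seen failed to attend.
- RAAC: (125 − 84)/125 = 41/125 = 32.8% (24.7% to 41.8%). This describes a clinic outside the listed comparison.

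**The case against.** The best defence is that the article is condensed and the denominator of the 2×2 table is inferred from the heading above the outcome. The objective is a comparison of search methods, the team did review 1436 records, and the full protocol may use them. This has some weight: the negatives exist, so specificity is not unobtainable in principle. But the article states the outcome, its groups, the eligibility rules and the consent route, and together these leave the negatives out.

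It is also fair that a specialist reference could yield negatives among the 84. Reduced medication was a possible clinic outcome, and only 22 went on to the SAAC. That makes the estimate defined, but still confined to pre-screened attenders.

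A third objection also stands: the 976 cannot simply be taken as true negatives. Some may have been uncontrolled but already under secondary care, the count conflicts with 369, and PRIMIS may have been the search that produced the 1436.

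On non-attendance, a reader might infer that the outcome cannot be estimated at all, or that the design hides a real difference between the service models. The documents support neither. The outcome is not limited to the index visit, later visits are recorded, the eligibility wording for outpatients is referral, and no outpatient non-attendance figure is given.

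**Conclusion.** The point holds for PRIMIS specificity in the groups as listed. There are 0 negatives against the record reference. Against specialist assessment there are at most 84 verified patients, all selected as record-positive, with perhaps 8 to 25 negatives under the assumed range. Sensitivity against the record criteria remains estimable, conditional on the initial search, provided PRIMIS was run separately from that search. The document does not say whether it was.

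The non-attendance point is narrower. Index-visit non-attendance is zero by construction in enrolled SAAC patients and in outpatients recruited from the attendance list. Follow-up non-attendance is estimable, though imprecise with about 20 patients per group. The fault is an undefined visit and denominator, together with the disagreement between referral and attendance as the basis of the outpatient group.

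Both outcomes are secondary. Neither affects exacerbation frequency or the sample size, so this should be corrected but does not threaten the main comparison.

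**What to change.** **PRIMIS**
1. State whether PRIMIS generated the initial search, and reconcile 460 with 369.
2. If it did not, build the 2×2 table from anonymised aggregate counts on all 1436 manually reviewed records. Separate records that failed the control criteria from those excluded for recent secondary care, and state that sensitivity and specificity are conditional on the initial search.
3. If it did, drop sensitivity and specificity. Report positive predictive value only: against record review (460/1436, subject to step 1), and against specialist assessment among the 84 attenders.

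**Non-attendance**
1. Report index-visit non-attendance for the SAAC and outpatient clinics from aggregate counts of booked appointments, confirming how many of the 22 were booked.
2. Report follow-up non-attendance separately in the enrolled groups.
3. Reconcile referral (Eligibility Criteria) with attendance (Recruitment) as the definition of the outpatient group.
4. Keep the RAAC figure of 41/125 as service description, outside this comparison.

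The cost is small: aggregate counts from practices and booking systems, a few lines of text, and possibly a minor approval to use anonymised counts.

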### Screening and Enrollment

#### Quantitative

All patients from the RAACs and all primary care patients will be approached for consent to use their anonymized data from the MISSION clinics or from GP records for research purposes. No extra data for research purposes will be collected for the quantitative analysis from patients at MISSION assessments, asthma outpatient clinics, or GPs.

#### Qualitative

##### Patients

All patients who attended MISSION SAACs will be approached to take part in qualitative one-to-one telephone interviews.

##### Health Care Professionals

Health care professionals who worked at the MISSION clinics from both primary and secondary care will be approached for qualitative interview. All health care professionals will be approached with an estimated 10 to be interviewed from primary care and 10 from secondary care. They will be contacted by email or telephone and, if interested, they will be sent a written information sheet by email or post. They will also be given contact details if they have any further questions regarding what is required to take part. If willing to take part, they will be sent a consent form to fill in and return to the study team.

### Recruitment

#### Modern Innovative Solutions to Improve Outcomes in Rapid Access Asthma Clinic and Severe Asthma Assessment Clinic Patients

All patients who attended the MISSION RAACs (quantitative) and SAACs (quantitative and qualitative) will be contacted by telephone to discuss the study and then, if they are interested, will be sent a patient information sheet (PIS) and consent form with a covering letter.

If the patient is unable to be contacted by telephone, they will be sent a covering letter from the MISSION team inviting them to take part in the study. They will be provided with a number to contact if they have any questions. They will be given the opportunity to read the PIS, and if they agree to take part in the study, they can return the consent form by post in a stamped addressed envelope.

#### Primary Care Patients

Patients in primary care will be contacted as described above.

#### Outpatient Severe Asthma Patients

Patients who attended outpatient clinics as new referrals in June and July will be approached by telephone after being identified from the clinic attendance list. If the patient is willing, they will be sent a PIS and consent form to send back to the study team in a stamped addressed envelope.

#### Health Care Professionals

Health care professionals who attended the MISSION RAACs or SAACs will be contacted by email or telephone to explain the study and then sent a PIS by email or post if they are interested in taking part. They will be given time to read the PIS, and if they wish to take part, they will be asked to return a consent form in a stamped addressed envelope.

### Quantitative Data Collection

Retrospective notes review at 6 months after the MISSION clinics will be performed to collect the following data. Data collected by study group are detailed in Table 1. Where information is not written in medical notes or clinic letters, it will be marked as not assessed.

**Table 1 table1:** Schedule of procedures at the Severe Asthma Assessment and Rapid Access Asthma Clinics.

Study group	MISSION^a^ Severe Asthma Assessment Clinics and outpatient severe asthma	MISSION Rapid Access Asthma Clinics and primary care patients
Full medical and asthma history	✓^b^	✓
Lung function testing	✓	✓
Inflammometry	✓	✓
Medication history	✓	✓
Health care usage (general practitioner attendances, emergency department attendances, and admissions)	✓	✓
Allergy status	✓	✓
Smoking status and history	✓	✓
Inhaler technique before and after review and documentation of improvements made	✓	✓
Disease-specific scores: Asthma Control Questionnaire and Asthma Quality of Life Questionnaire	✓	✓
Comorbidity screening: Epworth Sleepiness Scale, Sino Nasal Outcome Test -22, Hospital Anxiety and Depression Scale, Gastroesophageal Reflux Disease Questionnaire, and Nijmegen	✓	✓
Reviews by wider asthma multidisciplinary team, including time from referral to review	✓	X^c^

^a^MISSION: Modern Innovative Solutions to Improve Outcomes.

^b^✓: assessment performed.

^c^X: assessment not performed.

#### Modern Innovative Solutions to Improve Outcomes in Severe Asthma Assessment Clinic Patients and Outpatient Severe Asthma Patients

Retrospective notes review at 6 months after the MISSION clinics will be performed to collect the following data for MISSION SAACs and asthma outpatients. The clinical record form used for the MISSION SAACs is shown in Multimedia Appendix 2.

Where information is not written in medical notes or clinic letters, it will be marked as not assessed. Information will include the following:

Medical history including asthma history, asthma triggers, allergy history, past medical history, family history, and occupation.Lung function including peak flow, FEV1, FVC, transfer factor of the lung for carbon monoxide, CO transfer coefficient, and FeNO.Medication history including asthma and non-asthma medication.Exacerbation history including number of steroid courses, hospital admissions, and intensive treatment unit admissions.Health care usage including nonroutine GP attendances, OOH contacts, and ED attendances in 6 months pre- and post-MISSION SAAC or outpatient clinic.Allergy testing results and whether done.Smoking status, and if current smoker, whether any smoking cessation advice or referral was done.Inhaler technique—whether checked, any improvements made, and recommendations for inhaler devices.Investigations performed and time in days after first visit.ACQ score.AQLQ score.Sino nasal outcome test-22 (measure of sino nasal symptoms) score.Epworth sleepiness score (measure of somnolence, which can be caused by obstructive sleep apnea).Hospital anxiety and depression scale score.Nijmegen (assessment of hyperventilation syndrome) score.Gastroesophageal Reflux Disease Questionnaire (assessment of gastroesophageal reflux) score.Time of GP referral, first clinic visit, and second clinic visit.Time of referral and appointment with other specialities, for example, ENT, dietician, and physiotherapy.

#### Modern Innovative Solutions to Improve Outcomes in Rapid Access Asthma Clinics

Lung function including FEV1, FVC, peak flow, and FeNO.ACQ and AQLQ at baseline, 3 months, and 6 months in MISSION RAAC patients.Medication history for the last 12 months.Exacerbation history for the last 12 months.OOH, hospital, and emergency department attendances

### Qualitative Data Collection

#### Modern Innovative Solutions to Improve Outcomes Severe Asthma Assessment Clinic Patients

The target population for the qualitative telephone interviews is all of the 20 patients who attended the MISSION SAACs. All patients in this group will be approached for an interview. Participants from MISSION SAACs who are taking part in qualitative interviews will have 1 telephone interview as part of this evaluation research study.

Interviews will be arranged at a mutual date and time of convenience. The researcher will make the telephone calls to minimize costs to the participants and facilitate audio recordings. Interviews will be held in a semistructured manner using a topic guide with relevant prompts. This will allow patients to focus discussion on the issues important to them and hear their experiences and views in their own words with free discussion guided by the patient.

The areas explored will include the patients’ perceptions, understanding, fears, and concerns about their asthma as well as their views on MISSION—problems, barriers, and positive experiences. The interview will explore asthma and asthma service delivery.

The topic guide will be developed in conjunction with the payment protection insurance advisor.

